## STATISTICAL CONSIDERATIONS

### Estimating the number of patients needed

With a one-step Fleming plan, the calculation of the number of patients needed takes into account:

- The primary endpoint: severe toxicity at 2 years limited to 5-15%, minimum N is equal to 67 patients (unilateral,  $\alpha = 0.05$ ,  $\beta=0.10$ )
- and the secondary endpoint: 2-year local control of 80-90%, minimum N is equal to 83 patients (unilateral,  $\alpha = 0.05$ ,  $\beta=0.20$ )

In order to compensate for possible loss to follow-up, 90 patients will be included.

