### IV. RESEARCH DESIGN

#### IV.1. Primary endpoint

**Rate of patients with late toxicity at 2 years grade  $\geq 3$**  according to the NCI - CTCAE V4.03 classification in connection with hypofractionated stereotactic radiotherapy, i.e. grade  $\geq 3$  toxicities occurring beyond 3 months after the end of stereotactic radiotherapy.

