### 430 **V.3. Description of stop rules**

431 *V.3.1 Permanent or temporary cessation of a person's participation*

432 All patients included in this study will have the right to leave the study at any time, without having  
433 to justify the reason and without this calling into question their usual medical follow-up.

434 The reasons for leaving the study must be related to the following criteria:

- 435 • Withdrawal of consent: the patient will be free to stop the study at any time and without  
436 prejudice to his or her further treatment. The patient will have to specify whether he or she  
437 only wishes to stop the current treatment, or whether he or she also wishes to stop the  
438 monitoring provided for in the protocol or whether he or she wishes to have the data already  
439 collected in the database about him or her destroyed.
- 440 • Unacceptable toxicity attributed to treatment
  - 441 • Pregnancy
  - 442 • Non-compliance with the protocol
  - 443 • Patient lost to follow-up
  - 444 • Death.

445 *V.3.2 Premature discontinuation of study treatment*

446 Treatment may be discontinued prematurely for the following reasons:

- 447       • Toxicity
- 448       • Disease progression
- 449       • Refusal to continue the trial, withdrawal of consent

- Major breach of protocol.

Whenever possible, patients who have discontinued treatment prematurely will be monitored according to the protocol.

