### 535 ***VI.5.1 Assessment during immediate follow-up visits***

#### 536 **Follow-up visit at 14±3 days after the last stereotactic radiation therapy session**

- 537 • Clinical examination including weight  
 538 • Assessment of general condition according to WHO status  
 539 • Tumor bed examination (clinical +/- nasofibroscopy)  
 540 • Examination of the mouth, throat and neck

- 541 • Type of feed (Solid, liquid, mixed...)
- 542 • Acute toxicity assessments according to NCI-CTCAE v.4.03
- 543 • Collection of concomitant treatments

544

545 **Follow-up visit at 30±5 days after the last stereotactic radiotherapy session**

- 546 • Clinical examination including weight
- 547 • Assessment of general condition according to WHO status
- 548 • Tumor bed examination (clinical +/- nasofibroscopy)
- 549 • Examination of the mouth, throat and neck
- 550 • Type of feed (solid, liquid, mixed, etc.)
- 551 • Acute toxicity assessments according to NCI-CTCAE v.4.03
- 552 • Collection of concomitant treatments
- 553 • EORTC QLQ-C30 and H&N35 Questionnaire

554

555 **Follow-up at 3 months ±10 days after the last stereotactic radiation therapy session**

- 556 • Clinical examination including weight
- 557 • Assessment of general condition according to WHO status
- 558 • Tumor bed examination (clinical +/- nasofibroscopy)
- 559 • Examination of the mouth, throat and neck
- 560 • Type of feed (solid, liquid, mixed, etc.)
- 561 • Acute toxicity assessments according to NCI-CTCAE v.4.03
- 562 • Carcinologic evaluation:
  - 563 ❖ CT scan or cervicofacial MRI (*The choice between MRI and CT is left to the*
  - 564 *discretion of the investigator but follow-ups must be carried out with the same*
  - 565 *technique)*
  - 566 ❖ Chest CT scan (*The use of PET-FDG is left to the choice of the investigators in each*
  - 567 *center if it is medically indicated)*

568

569

570 **VI.5.2 Assessment during long-term monitoring visits**

571 These visits will take place every **3 months±10 days for up to 2 years** after stereotactic radiotherapy

572 and include:

- 573 • Clinical examination including weight
- 574 • Assessment of general condition according to WHO status
- 575 • Tumor bed examination (clinical +/- nasofibroscopy)

- 576 • Examination of the mouth, throat and neck
- 577 • Type of feed (solid, liquid, mixed, etc.)
- 578 • Late toxicity assessments according to NCI-CTCAE v.4.03
- 579 • Carcinologic assessment at **12 months and 24 months**

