### 588 ***VI.5.3 Follow-up on recidivism***

- 589 In the event of local, regional, locoregional or distant recurrence, patients will be monitored only for
- 590 their vital status.
- 591 Data from salvage treatments will be collected in the CRF.
- 592

Table 1: Flow chart

| PERIODE DE L'ESSAI                                                                                                                                                                                                                                                                                                                                                                                                                   | BILAN A L'INCLUSION                  | SUIVI PENDANT LA RADIOTHERAPIE |       | VISITES DE SUIVI POST RADIOTHERAPIE STEREOTAXIQUE |            |                  |                                |                 |                   |                   |                   |                   |                   |
|--------------------------------------------------------------------------------------------------------------------------------------------------------------------------------------------------------------------------------------------------------------------------------------------------------------------------------------------------------------------------------------------------------------------------------------|--------------------------------------|--------------------------------|-------|---------------------------------------------------|------------|------------------|--------------------------------|-----------------|-------------------|-------------------|-------------------|-------------------|-------------------|
| Visites n°                                                                                                                                                                                                                                                                                                                                                                                                                           | V0                                   | V1                             | V2    | V3                                                | V4         | V5               | V6                             | V7              | V8                | V9                | V10               | V11               | V12               |

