| Test de grossesse doit être réalisé dans les 14 jours maximum avant le début de la radiothérapie stéréotaxique
Scanner thoracique: A refaire à l'inclusion uniquement si le délai entre le scanner thoracique préopératoire et la date de début de la radiothérapie est supérieur à 3 mois.
En cas de récurrence locale, régionale, locorégionale et/ou à distance, les patients seront suivis uniquement pour le statut vital |                                      |                                |       |                                                   |            |                  |                                |                 |                   |                   |                   |                   |                   |

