### 933 **IX.3. Main analysis**

934 The analysis of the main objective, i.e. the rate of severe toxicity of grade  $\geq 3$  to 2 years, with its 95%  
 935 CI will be compared to 15% (with regard to the assumptions set in the context of the estimation of  
 936 the number of subjects needed). If the 95% CI does not include this rate, the trial will be considered  
 937 positive. For efficacy endpoints, 95% bilateral confidence intervals will be provided. Statistical  
 938 analysis will be performed on an intention-to-treat basis.

939 An analysis of the predictive factors of severe toxicity of grade  $\geq 3$  to 2 years will be performed. A  
 940 univariate analysis will be performed using the usual tests: Student's test or Mann-Whitney test if the  
 941 conditions of the t-test are not met (normality, and homoscedasticity studied by the Fisher-Snedecor  
 942 test) for quantitative variables and Chi2 test or Fisher's exact test for categorical variables. The  
 943 multivariate analysis will consider a logistic regression model for binary dependent variable.  
 944 Covariates will be retained based on the results of univariate analysis and their clinical relevance.

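### Scheduled toxicity follow-up stops at any recurrence, and the protocol does not say how those patients enter the 2-year toxicity rate

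*Protocol*

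**What the plan says.** - **Endpoint (IV.1):** "Rate of patients with late toxicity at 2 years grade" ≥3, related to the stereotactic treatment and arising more than 3 months after it ends.
- **Collection (VI.5.2):** the visits every 3 months up to 2 years include "Late toxicity assessments according to NCI-CTCAE v.4.03".
- **After recurrence (VI.5.3):** "In the event of local, regional, locoregional or distant recurrence, patients will be monitored only for" vital status; data on salvage treatment are also collected. The footnote to the flow chart (Table 1) repeats the restriction: "les patients seront suivis uniquement pour le statut vital".
- **Analysis (IX.3):** the rate with its 95% "CI will be compared to 15% (with regard to the assumptions set in the context of the estimation of" sample size. The trial is positive if the interval excludes 15%, and "analysis will be performed on an intention-to-treat basis". IX.1 adds a count rule: 6 or more of 67 is unacceptable.
- **Missing data (IX.5):** an attrition sensitivity analysis is planned, from which an imputation method will be chosen. Maximum bias and multiple imputation are among the options.
- **Time-to-event methods (IX.2):** Kaplan-Meier estimation is described with recurrence-free survival, overall survival and quality-of-life deterioration as examples. Late toxicity is not named.
- **Serious adverse events (XI.2.1, XI.2.3):** reportable for every included patient until 2 years after radiotherapy, with no stop at recurrence.

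**The concern.** Observation of the primary endpoint ends because of another outcome. A patient with an isolated nodal or lung relapse at month 6 has an irradiated operating bed and up to 18 further months at risk, but no scheduled toxicity visit. The intention-to-treat denominator keeps that patient.

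The simplest calculation, observed toxicities over all included patients, turns unseen events into non-events. For a safety endpoint this is anti-conservative, because it lowers the rate and helps exclude 15%. Local control, which sets the 83-patient requirement, has the same gap: a local failure after a first regional or distant recurrence falls outside scheduled follow-up.

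**Working it through.** **1. The plan's own sizes.** One-stage formula: n = [(z₁₋α√(p₀(1−p₀)) + z₁₋β√(p₁(1−p₁)))/(p₁−p₀)]².
- Toxicity, p₀ = 0.05, p₁ = 0.15, one-sided α = 0.05, power 90%: 66.6, so 67. Reproduced.
- Local control, p₀ = 0.80, p₁ = 0.90, one-sided α = 0.05, power 80%: 82.9, so 83. Reproduced.

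**2. The decision limit at N = 90.** IX.3 does not name the interval method. The exact two-sided 95% interval is 2.5%–13.9% for 6/90 and 3.2%–15.4% for 7/90. The Wilson upper limit for 7/90 is 15.2%. So at most 6/90 excludes 15% under either method. With a true rate of 15% and full observation, P(X ≤ 6 | 90, 0.15) = 1.3%.

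**3. Dilution if unseen toxicity is scored as none.** The protocol gives no total recurrence rate, so these inputs are assumptions:
- True 2-year rate p = 0.15, the limit in IX.3.
- Onset of toxicity uniform over months 3–24, so mean onset is 13.5 months.
- A share f of patients has observation cut short by recurrence, at a time uniform over 0–24 months and independent of toxicity. The range is f = 10–35%. For orientation, IX.1 plans for local failure of 10–20% alone, and the brachytherapy series of tongue cancers cited in I.2.1 has 2-year local control of 79% and overall survival of 72%.

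Among patients who relapse, the chance that recurrence precedes the toxicity is 13.5/24 = 0.5625. The expected observed rate is therefore q = 0.15 × (1 − 0.5625 f).

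| f | q | P(≤6/90), interval excludes 15% | P(≤5/67), count rule of IX.1 | Patients not cut short, of 90 |
|---|---|---|---|---|
| 0 | 15.0% | 1.3% | 5.1% | 90 |
| 10% | 14.2% | 2.2% | 7.4% | 81 |
| 20% | 13.3% | 3.6% | 10.4% | 72 |
| 35% | 12.0% | 7.2% | 16.7% | about 59 |

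The probabilities are binomial with success rate q. A patient who dies without toxicity cannot develop it later and is a legitimate non-event, so deaths are not counted as bias. The 35% row is an upper bound, because a share that large could be reached only by including patients who soon die.

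**4. How much the unfixed rule matters.** Take N = 90, 18 patients with incomplete observation, and 4 observed toxicities:
- Missing counted as none: 4/90 = 4.4% (exact 95% interval 1.2%–11.0%).
- Complete cases: 4/72 = 5.6% (1.5%–13.6%).
- Missing counted as toxic: 22/90 = 24.4% (16.0%–34.6%).

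The first two lie wholly below 15% and the third wholly above it. The handling rule alone can decide the trial.

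**The case against.** The strongest reply is that nothing in the protocol scores an unobserved patient as free of toxicity. Intention to treat fixes the denominator, not the value given to a missing outcome. IX.5 leaves the method open, and counting missing as toxic would push the rate up. An analysis plan is announced and may settle this. That stands against reading the crude count as the stated rule. It does not answer the main point, since no analysis plan can recover observations the protocol says not to make.

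Second, serious-event reporting runs to 2 years and would capture some post-recurrence events. That also stands, in part. Grade 3 is not the same as serious, XI.1.2 exempts hospitalisation or surgery for the disease from reporting, and the requirement conflicts with following vital status only.

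Third, stopping at recurrence has a rationale: after salvage to the same bed, attribution to the study treatment is uncertain. This does not cover an isolated nodal or distant relapse with no salvage to the operating bed.

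A reader might also infer two stronger points that the protocol does not support.
- V.3.1 lists "Unacceptable toxicity attributed to treatment" as a reason to leave the study, which might seem to hide the targeted events. But a patient leaving for grade ≥3 late toxicity has already had the event and is counted. Only departures for acute toxicity could lose later events, and V.3.2 keeps patients who stop treatment early under monitoring where possible.
- The synopsis says "In order to compensate for possible loss to follow-up, 90 patients will be included", and 90 − 83 = 7 might look like the whole margin. The 83 belongs to local control. The toxicity endpoint needs 67, so its margin is 90 − 67 = 23.

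**Conclusion.** The point holds in a limited form. The protocol ends scheduled toxicity assessment at any recurrence, does not fix how the affected patients enter the primary rate, and conflicts with its own serious-event reporting period. Under a crude count the bias is downward and favours a positive trial.

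On the assumptions shown, the size is modest: the false-positive chance under the interval rule goes from 1.3% to between 2.2% and 7.2%, and exceeds 5% only toward the top of the range. The larger figures obtained with a limit of 7/90 do not describe the trial's rule, since exact and Wilson intervals at 7/90 still include 15%. The conclusion depends on the assumed recurrence share and timing; at 10% the effect is small. It is worth correcting because the correction is cheap and the lost data cannot be restored at analysis.

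**What to change.** 1. Amend VI.5.3 and the flow-chart footnote so that, in patients alive after recurrence, grade ≥3 late toxicity and local status are still recorded to month 24. Record salvage dates and site, and show post-salvage events separately.
2. Estimate the primary endpoint in irradiated patients as a 2-year cumulative incidence of first grade ≥3 late toxicity. Treat death as a competing event, censor patients whose toxicity follow-up ends early, and compare the upper confidence limit with 15%. Censoring assumes that these patients have the same later toxicity risk as those still observed, which is a further reason for step 1.
3. Reconcile VI.5.3 and the footnote with the analysis set in IX.3, the missing-data text in IX.5 and the reporting period in XI.2.

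The cost is a short amendment and some additional case report form data. The main drawback is that toxicity after salvage to the operating bed will be hard to attribute, hence the separate display.

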#### IV.2. Secondary endpoints

- **Local control at 2 years.** Will be considered as an event: local recurrence (T) documented in the area of the operating bed. The diagnosis of local recurrence requires histological confirmation.
- **Locoregional control at 2 years.** The following are considered to be events: local recurrence (T) and/or lymph node recurrence (N), i.e. ipsilateral or contralateral cervical positive lymphadenopathy(es). The diagnosis of regional recurrence requires confirmation by imaging and/or histologic.
- **Grade  $\geq 3$  acute toxicity** (toxicities occurring during treatment up to  $\leq 3$  months after the end of treatment) in connection with hypofractionated stereotactic radiotherapy, according to the NCI classification - CTCAE V4.03
- **2-year recurrence-free survival (RSS):** defined as the time interval between the date of inclusion and the date of the first cancer event (local recurrence, regional recurrence, distant metastasis) or death from any cause.

- 385 • **2-year overall survival (OS):** defined as the time interval between the date of inclusion and
- 386 the date of death from any cause.
- 387 • **Quality of Life (QoL):** according to the EORTC QLQ-C30 and EORTC-H&N35
- 388 questionnaires
- 389 • **Nutritional impact,** assessed by patient weight and feeding tube use.
- 390 • **Predictive factors of toxicity at 2 years :** clinical and/or dosimetric factors associated with
- 391 late severe toxicity.

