## VI.8. Effectiveness evaluation

### VI.7.1 Locoregional control

626 Evaluation of the tumor bed (clinical +/- nasofibroscopy) and cervical lymph nodes will be  
627 performed in accordance with the table of investigations and evaluations (see Table 1).

628 Evaluation by imaging (+/- panendoscopy) will be repeated as soon as appropriate in case of clinical  
629 doubt about tumor recurrence. Imaging evaluation will be systematic at 3 months, 1 year and 2 years  
630 after the end of radiotherapy.

631

632 • **Local recurrence**

633 Recurrence will be considered local if documented in the operative bed area. The diagnosis of local  
634 recurrence requires histological documentation. The date of recurrence will therefore be equal to the  
635 date of the biopsy that allowed histological confirmation.

636 • **Regional recidivism**

637 Recurrence will be considered regional if it occurs in the form of positive lymphadenopathy at the  
638 ipsilateral or contralateral cervical level

639 The diagnosis of a regional recurrence requires confirmation by imaging (CT scan and/or MRI and/or  
640 PET-FDG) and/or histological. The date of regional recurrence will be the date of the CT scan or  
641 MRI or PET – FDG highlighting the progression or the date of the biopsy in case of histological  
642 confirmation.

643 If histological confirmation of regional recurrence cannot be obtained, the diagnosis may be made  
644 based on the investigator's judgment.

645 **VI.7.2 Remote Recidivism**

646 The remote diagnosis of recurrence will be performed when one of the following criteria is met:

- 647 • Clear radiological evidence of distant metastasis on imaging (CT or MRI or PET – FDG)
- 648 • Positive biopsy (in case of radiological doubt or clinically suspected recurrence such as skin  
649 metastasis or palpable mass)

650 The date of distant recurrence will be the date of the CT scan or MRI or PET – FDG highlighting the  
651 metastases or the date of the biopsy in case of histological confirmation.

652 If histological confirmation of distant recurrence cannot be obtained, the diagnosis may be made  
653 based on the investigator's judgment.

654

655 **VI.7.3 Second cancer**

656 The diagnosis of a second cancer requires histopathological evidence of a new tumor mass outside  
657 the operative bed area, which is not consistent with the diagnosis of local recurrence or regional lymph  
658 node recurrence.

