### IX.1. Number of topics to include

881 To determine the number of patients needed, two objectives were considered: severe late toxicity at  
882 2 years (primary outcome) and local control rate at 2 years (secondary outcome). The experimental  
883 design follows a one-step Fleming design with no intermediate analysis due to the primary endpoint  
884 which will be evaluated at 2 years (severe late toxicity).

885 The safety and efficacy profile of hypofractionated stereotactic radiotherapy of the operative bed is  
886 expected to be equivalent to other radiotherapy techniques (brachytherapy or normofractionated  
887 IMRT) (cf 3. Rationale of the study for details). In brachytherapy, the rate of late soft tissue ulceration  
888 is around 10-20% and the rate of bone necrosis is around 5-10%. We have decided: 1/ to accept a rate  
889 of less than 5% and 2/ to reject a rate of more than 15%. With a unilateral test for significance ( $\alpha=0.05$ )  
890 with a power of 90% ( $\beta=0.10$ ), the minimum number of patients to be included is 67.  
891 Hypofractionated stereotactic radiotherapy of the operative bed will then be considered an  
892 unacceptable treatment if 6/67 patients (9%) or more have severe late toxicity (grade  $\geq 3$ ).

893 The local control rate of hypofractionated stereotactic radiotherapy is expected to be equivalent to  
894 other radiotherapy techniques (brachytherapy or normofractionated IMRT). We have decided: (i) to  
895 accept a rate of more than 90% and (ii) to reject a rate of less than 80%. With a one-sided significance  
896 test ( $\alpha=0.05$ ) with a power of 80% ( $\beta=0.20$ ), the minimum number of patients to be included is 83.  
897 A lower potency was decided for control as a secondary outcome. Hypofractionated stereotactic  
898 radiotherapy of the operative bed will then be considered an acceptable treatment if 72/83 patients  
899 (87%) or more are locally controlled at 2 years.

900 As a result of these results, and to compensate for possible loss to follow-up, a total of 90 patients  
901 will be included in this study.

902 As the primary objective of this study is estimated at 2 years, once 30 patients have been included  
903 (33% of inclusions), a review of all grade  $\geq 3$  toxicities will be communicated to the independent trial  
904 monitoring committee (IDSMC = *Independent Data and Safety Monitoring Committee*). The grade 4  

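### Follow-up drops to vital status after any recurrence, so bed relapses that follow a regional or distant recurrence are not systematically recorded, and the crude 72/83 local-control count can read too high

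*Protocol*

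**What the plan says.** **Follow-up rule.** Protocol VI.5.3: "In the event of local, regional, locoregional or distant recurrence, patients will be monitored only for" vital status. The footnote to Table 1 says the same in French: "les patients seront suivis uniquement pour le statut vital". The one other item kept after recurrence is in VI.5.3: "Data from salvage treatments will be collected in the CRF".

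**Endpoint.** IV.2 on local control at 2 years: "Will be considered as an event: local recurrence (T) documented in the area of the operating bed". VI.7.1 (printed under VI.8) agrees: "Recurrence will be considered local if documented in the operative bed area". Both require histology. Neither limits the event to a first recurrence. In the same list, recurrence-free survival is explicitly tied to the first cancer event or death.

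**Schedule.** VI.7.1 says that evaluation of the bed and neck nodes is "performed in accordance with the table of investigations and evaluations (see Table 1"), the table that carries the vital-status footnote.

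**Decision rule.** IX.1 sets the limits for local control: "accept a rate of more than 90% and (ii) to reject a rate of less than 80"%. It uses a one-sided 5% test with 80% power and needs 83 patients. The "radiotherapy of the operative bed will then be considered an acceptable treatment if 72/83 patients" or more are locally controlled at 2 years.

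**The concern.** Ending local assessment at the first recurrence of any kind suits recurrence-free survival and overall survival. It does not suit an endpoint that counts every bed recurrence within 2 years. Once a patient has a nodal or distant recurrence, the protocol no longer asks for bed examination, imaging or biopsy. A later bed relapse enters the data only if the salvage-treatment record happens to show it. Locoregional control has the same gap for nodal relapse after a distant recurrence.

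Local control is secondary, but it sets the larger sample size (83, against 67 for toxicity) and has its own acceptance threshold. If hidden relapses count as controls, the error favours accepting a treatment whose local control is at the rejection limit. An analysis plan can choose how to classify these patients. It cannot recover bed status that was not collected.

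**Working it through.** **1. The plan's own figure.** With 80% against 90%, one-sided alpha 0.05 and power 80%, the normal-approximation formula gives

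n = [(1.645·√(0.8·0.2) + 0.842·√(0.9·0.1)) / 0.1]² = 82.89, rounded up to 83.

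This reproduces IX.1. Under the exact binomial, the rule of at least 72/83 passes with probability 7.6% at a true 80% and 87.7% at a true 90%. The 7.6% is the baseline below. That it exceeds 5% comes from the cut-off and is a separate matter.

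**2. Inputs the documents do not give.** Let q be the share of patients with a regional or distant recurrence first, and s the share of those who later relapse in the bed within 2 years. Both are assumptions. I take q = 10–15% and s = 10–20%, so q·s runs from 0.10·0.10 = 1 point to 0.15·0.20 = 3 points. One hidden relapse in 83 is 1/83 = 1.2 points.

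**3. These patients counted as controlled** (the literal reading of a crude count of documented bed recurrences). Apparent control = 80% + q·s, and the chance of acceptance is P(X ≥ 72 | 83, apparent control):

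| Hidden failure | Apparent control | Chance of reaching 72/83 |
|---|---|---|
| 0 points | 80% | 7.6% |
| 1 point | 81% | 11.3% |
| 2 points | 82% | 16.3% |
| 3 points | 83% | 22.7% |

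With wider assumptions (q = 5–20%, s = 10–30%) the shift is 0.5 to 6 points and the chance runs from 9.3% to 50.0%.

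**4. Censored at the first non-local recurrence.** Assume constant hazards and ignore death. The non-local recurrence hazard is a = −ln(1−q)/2. The local hazard is l before that recurrence and h = HR·l after it. With k = a + l − h, solve for l so that true 2-year control is 80%:

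exp(−2(a+l)) + a·exp(−2h)·(1 − exp(−2k))/k = 0.80.

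The censored estimate is then exp(−2l):

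| q | HR = 1 | HR = 2 | HR = 3 |
|---|---|---|---|
| 10% | 80.0% | 80.8% | 81.5% |
| 20% | 80.0% | 81.6% | 82.9% |

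There is no bias if local risk is unchanged and an upward bias if it rises. By the same formula the bias is downward if the risk falls.

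**5. Excluded as not evaluable.** Apparent control = 1 − (0.20 − q·s)/(1 − q). At q = 15%, s = 10% this is 1 − 0.185/0.85 = 78.2%. At q = 10%, s = 20% it is 1 − 0.18/0.90 = 80.0%. The bias is upward only if s exceeds 20%.

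**6. Counted as failures.** Apparent control = 0.80 − q·(1 − s). At q = 15%, s = 10% this is 66.5%. At q = 10%, s = 20% it is 72.0%. The bias is downward.

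**The case against.** The strongest reply is that the protocol does not say how a patient with an earlier regional or distant recurrence is classified for local control. That choice is commonly left to an analysis plan. Steps 4 to 6 show that the direction depends on it. A reader might infer that local control is biased upward whatever is done. The documents do not support that, and this part of the objection stands. So does the point that q and s appear nowhere in the protocol: 1 to 3 points is roughly 1 to 2.5 patients in 83. Nor do the documents show that local risk rises after a first recurrence, since salvage treatment could move it either way.

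A reader might also infer that later bed relapses are never recorded. That is too strong, because salvage-treatment data are collected and may reveal some. A bed relapse found together with a nodal or distant recurrence is captured too.

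The consequence also has limits. IX.3 ties a positive trial to late toxicity against 15% and plans two-sided 95% intervals for efficacy. IX.2 calls the trial exploratory. The published local-control rates in I.2.1 (79%, 81%, 85%) may rest on a first-event convention, which cannot be checked here.

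None of this closes the gap. IV.2 and VI.7.1 define an endpoint that the follow-up rule stops measuring in some patients. Each way of classifying them substitutes a convention for the missing observation.

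**Conclusion.** The follow-up rule and the local-control definition do not fit together. Bed recurrences after a regional or distant recurrence, and nodal recurrences after a distant one, are not systematically recorded. Under the crude 72/83 count, with only documented bed recurrences as events, the bias is upward for any such hidden relapse. Under censoring it is upward only if local risk rises after the first recurrence. Under exclusion it is nil or downward on the assumed ranges, and under failure-counting it is downward.

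The size cannot be derived from the documents. The rise from 7.6% to 11.3–22.7% illustrates 1 to 3 hidden points with these patients counted as controlled. It is not an estimate for this trial. Because the endpoint is secondary and the size unknown, this is a cheap improvement. It does not show that the local-control result will be wrong. A reader might conclude that the 72/83 rule must be dropped, but that does not follow. It is enough to state what the result covers.

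**What to change.** Amend VI.5.3 and the Table 1 footnote. After a regional or distant recurrence without local recurrence, keep recording operative-bed status in the eCRF from routine care: recurrence yes or no, date, and whether confirmed by histology. After a distant recurrence, record nodal status in the same way. Continue until local recurrence, death or 24 months. No procedure is added.

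The cost is a short amendment, one eCRF page and some extra data entry for the patients concerned. Routine-care recording will be less uniform than scheduled visits. Keeping histological confirmation as its own field makes relapses without biopsy visible.

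If this is not done, label the endpoint *local recurrence as first event*. Report it as a cumulative incidence with other recurrences and death as competing events, and state that the 72/83 result does not cover later bed recurrences.
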